### Sample size

According to the study by Baqeri et al. [11], the average sexual satisfaction of spouses in the intervention group before intervention was 2.47 ± 81.30 and after intervention was 2.28 ± 82.70. Considering an alpha of 0.05 and 80% power, the sample size was estimated to be 45 couples in each of the two intervention and control groups. Taking into account potential sample attrition in each study arm (intervention and control), approximately 50 couples will be selected and included in the study.$$=\frac{{\left({z}_{1-\frac{\propto }{2}}+{z}_{1-\beta }\right)}^{2}\times {{\sigma }_{1}}^{2}+{{\sigma }_{2}}^{2}}{{\left({\mu }_{1}-{\mu }_{2}\right)}^{2}}=\frac{{\left(1.96+0.58\right)}^{2}\times {2.28}^{2}+{2.47}^{2}}{{(82.70-81.30)}^{2}}=\frac{7.89\times 5.19+6.10}{1.96}=45$$

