**Method:**

This study is a clinical randomized controlled trial. Sampling will be done on a convenience basis. Participants will be randomly allocated into two groups: control (50 couples) and intervention (50 couples). Couples in 6 groups of 8 members each will attend counseling sessions based con the CHARMS model, with sessions held weekly and lasting for 60 min. Data collection tools will include Demographic information questionnaire, Women’s Sexual Quality of Life Questionnaire, Enrich Marital Satisfaction Questionnaire, Sexual Compatibility Questionnaire and Perceived Quality of Relationship Dimensions Questionnaire, which will be completed by women in both groups before and after the intervention. Data will be analyzed using appropriate statistical tests and SPSS software.

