### General objective

To determine the impact of couple counseling based on the CHARMS model on sexual quality of life and marital satisfaction of wives of men with myocardial infarction.

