### Research hypothesis

Couple counseling based on the CHARMS model leads to an increase in the average score of sexual quality of life and marital satisfaction in wives of men with myocardial infarction.

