### Data analysis

Descriptive analysis will be utilized to present baseline characteristics. Independent t-tests/Mann-Whitney tests will be employed to compare normal/abnormal quantitative variables between two groups, while paired t-tests/Wilcoxon tests will assess the intervention’s impact on normal/abnormal quantitative variables. Chi-square tests will be used to compare qualitative variables between groups, and Mac-Nemar tests will evaluate the intervention’s effect on qualitative variables. The Kolmogorov-Smirnov test will assess the normality of data distribution for quantitative variables. If needed, other statistical tests like regression models may be applied. Statistical analyses will be conducted using SPSS 22, with a significance level of 5% considered.

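### The 80% power for 45 couples per arm rests on a one-arm before/after change in sexual satisfaction, so it is unsupported for the trial's between-arm comparison of its own outcomes

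*Protocol article*

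**What the plan says.** The Sample size section of the protocol article cites an earlier study in which "the average sexual satisfaction of spouses in the intervention group before intervention was 2.47 ± 81.30 and after intervention was 2.28 ± 82.70". The figures are printed as SD ± mean. They are used as the two means and two SDs of a formula for comparing independent groups, with this conclusion: "Considering an alpha of 0.05 and 80% power, the sample size was estimated to be 45 couples in each" arm. For attrition, "approximately 50 couples will be selected and included in the study". The Abstract makes clear that this is a per-arm number: "Participants will be randomly allocated into two groups: control (50 couples) and intervention (50 couples").

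The General objective is to find the effect of counselling "on sexual quality of life and marital satisfaction of wives of men with myocardial infarction", and the Research hypothesis is that "Couple counseling based on the CHARMS model leads to an increase in the average score of sexual quality of life and marital satisfaction". For the comparison of arms, the Data analysis section states: "Independent t-tests/Mann-Whitney tests will be employed to compare normal/abnormal quantitative variables between two groups". Data collection tools lists a sexual quality of life questionnaire (18 to 108) and a marital satisfaction questionnaire (47 to 235) for these outcomes. It lists no questionnaire named for sexual satisfaction.

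**The concern.** A sample size for a two-arm comparison needs the expected difference between the arms and the spread of the outcome to be compared. The section supplies neither. The 1.40 is what one treated arm gained from before to after. That gain includes whatever a control arm would also gain, for instance from recovery over time or from repeating the questionnaire. The two SDs are those of the same arm at two time points, used as if they came from two separate arms. The variable also differs by name from both outcomes in the hypothesis.

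What is at stake is how the result can be read. The Discussion section plans to learn from negative results as well as positive ones. That requires knowing what difference on the trial's own outcomes the trial could have detected, and the section does not say.

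**Working it through.** **Inputs (Sample size section).** Before: mean 81.30, SD 2.47. After: mean 82.70, SD 2.28. Alpha 0.05, two-sided (1.96 in the formula). Target power 80%. Planned number 45 per arm, about 50 with attrition.

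**Step 1: reproduce the plan's figure.**
- Formula: n per arm = (z for alpha + z for power)² × (SD1² + SD2²) / difference².
- Variances: 2.28² + 2.47² = 5.198 + 6.101 = 11.299. Difference: 82.70 − 81.30 = 1.40, and 1.40² = 1.96.
- With z = 1.96 and 0.84: 7.84 × 11.299 / 1.96 = 45.2.
- With the plan's rounded values and brackets around the variances: 7.89 × (5.19 + 6.10) / 1.96 = 45.4.

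So 45 reproduces; rounded up, it is 46.

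**Step 2: the line as printed.**
- The z for power is printed as 0.58, but (1.96 + 0.58)² = 6.45, whereas the next step prints 7.89. A z of 0.85 gives 2.81² = 7.896, which matches.
- The variance sum is printed without brackets. Read literally, (7.89 × 5.19 + 6.10) / 1.96 = 24.0.
- The printed 7.89 and the result of 45 show that the calculation used a z of about 0.85 and a bracketed sum. Both faults are misprints.

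**Step 3: power at the plan's own effect.**
- Pooled SD = √(11.299 / 2) = 2.377. Standardised effect = 1.40 / 2.377 = 0.59.
- Power of a two-sided 5% independent t test: 78.9% at 45 per arm, 79.8% at 46, 83.0% at 50. The normal approximation gives 79.8% at 45.

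**Step 4: what the 80% depends on.** The between-arm difference is the intervention arm's change minus the control arm's change. The document gives no control-arm change, so the gains below are assumptions. SD 2.377, t test:

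| Assumed control gain (points) | Between-arm difference | Standardised | Power at 45 per arm | Power at 50 per arm |
|---|---|---|---|---|
| 0 | 1.40 | 0.59 | 79% | 83% |
| 0.35 | 1.05 | 0.44 | 54% | 59% |
| 0.50 | 0.90 | 0.38 | 43% | 47% |
| 0.70 | 0.70 | 0.29 | 28% | 31% |

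A decline in controls would make the difference exceed 1.40 and raise power above the first row. Retaining all 50 couples per arm adds 3 to 5 percentage points.

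**Step 5: what the planned numbers detect whatever the scale.** With 80% power (two-sided 5%, independent t test, women treated as independent), 45 evaluable women per arm detect 0.60 SD and 50 detect 0.57 SD. The document gives no SD for either outcome, so these cannot be turned into points from it.

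**The case against.** Four points can be made for the plan.

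- **The calculation is sound apart from misprints.** This stands. A reader might infer from the printed line that the true answer is 24, or that z = 0.58 means the trial was sized for about 72% power. The document does not support that: its own 7.89 and 45 show that neither reading entered the result. The step from 45 to 46 has no consequence with about 50 per arm planned.
- **Using a related measure for planning is common.** This stands in part. The sexual quality of life questionnaire has a section on satisfaction with the relationship and sexual activity, and the cited study's instrument is not visible here. The fair criticism is that the link is not justified, not that it is shown to be wrong. For the same reason, 1.40 raw points should not be set against a guessed SD on another scale to produce a very low power. Only the standardised effect could carry over.
- **The control-gain figures are assumed.** This stands. They are illustrations, and power could also be higher than stated. A reader might infer that the trial is underpowered; the document does not show that either.
- **Nothing in conduct or analysis changes.** This also stands, and it limits the weight of the point.

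None of this answers the central defect: a within-arm change is used as a between-arm difference, with no control figure and no stated assumption that controls stay constant.

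**Conclusion.** The concern holds as a fault in the planning assumption, not in the arithmetic. The stated 80% power is unsupported for the comparison that the trial will make. It is correct, to within rounding, only under two unstated conditions: the control arm does not change, and a standardised effect of 0.59 applies to sexual quality of life and to marital satisfaction. If the first condition fails by half of the assumed gain (0.70 of 1.40 points), power at 45 per arm falls from 79% to 28%. A change in the opposite direction would raise it. These figures rest on the protocol's SDs and on assumed control gains, so the document fixes neither the true power nor a corrected sample size.

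**What to change.** Keep the planned numbers and rewrite the paragraph:

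1. Withdraw the power claim based on the 1.40 before/after change.
2. State that 45 evaluable women per arm give 80% power (two-sided 5%, independent t test, women treated as independent) for a between-arm difference of about 0.60 SD on each of the two outcomes, or 0.57 SD at 50 per arm. Convert this to points with each questionnaire's own SD, with a source for that SD.
3. Say why a difference of that size is plausible and worth detecting. The detectable difference alone does not show this.
4. Note that counselling is delivered in groups of 8, and that any clustering this causes would make the detectable difference larger.
5. If the formula is kept, correct the z for power to about 0.84 to 0.85, bracket the variance sum, and report 46.

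The cost is one rewritten paragraph and a less favourable stated figure. No extra couples are needed.

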### Data collection tools

The following questionnaires will be used to collect data in this research.

Demographic information questionnaire: This tool includes demographic characteristics of the participants such as age, spouse’s age, duration of marriage, number of children, education level, spouse’s education level, employment status of the couple, family income sufficiency, current contraceptive method, duration of illness, age of first heart attack, medications used, and stage of heart disease in men.

Women’s Sexual Quality of Life Questionnaire: This tool measures the relationship between sexual dysfunction and women’s quality of life. It consists of 18 items divided into four main sections including psychological-sexual feelings, satisfaction with relationship and sexual activity, feelings of worthlessness, and sexual suppression. Scoring is based on a Likert scale ranging from 1 to 6, indicating from strongly agree to strongly disagree. The total score will range from 18 to 108, where a higher score reflects higher sexual quality [19, 20].

Enrich Marital Satisfaction Questionnaire, consisting of 47 questions. The minimum score is 47 and the maximum is 235. Scores below 115 indicate low marital satisfaction, 116 to 230 indicate moderate satisfaction, 231 to 345 indicate high satisfaction, and 346 to 460 indicate ideal satisfaction [21].

Sexual Compatibility Questionnaire: This questionnaire consists of 5 questions and aims to assess the level of sexual compatibility between couples. It is scored on a 5-point Likert scale. Higher scores indicate higher sexual compatibility. Scores below 8 indicate low sexual compatibility, scores between 9 and 16 indicate moderate compatibility, and scores above 17 indicate high sexual compatibility [22].

Perceived Quality of Relationship Dimensions Questionnaire: This scale consists of 18 questions and 6 subscales evaluating satisfaction, commitment, intimacy, trust, passion, and love. The minimum score is 18 and the maximum is 126. Lower scores indicate lower quality and higher scores indicate better quality of marital relationship in different dimensions [23, 24].

### Validity and reliability of questionnaires

Women’s Sexual Quality of Life Questionnaire: This tool has been translated, validated, and culturally adapted in Iran by Masoumi et al. (2013), demonstrating good validity, high internal consistency, and high reliability. It had a Cronbach’s alpha coefficient of 0.73 and an internal consistency of 0.88 (ICC = 0.88) [25].

The Enrich Marital Satisfaction Questionnaire: The validity and reliability of this tool in Iran were confirmed by Masoumi et al. (2021) with a validity of 0.86 and a reliability of 0.80 [21].

The Sexual Compatibility Questionnaire: In the study by Rashan Chesli et al. (2014), formal and content validity were assessed and approved by experts and professors. The reliability was calculated using Cronbach’s alpha, yielding a value of 0.91 [22].

The Perceived Quality of Relationship Dimensions Questionnaire: This scale, translated by Nilforoushan et al., had its content validity confirmed with a Cronbach’s alpha of 0.95 [24].

### Sampling and data collection

Samples will be selected using convenience sampling and divided into two groups: intervention (45 couples) and control (45 couples) based on even and odd numbers in sealed envelopes. The participants will be asked to choose an envelope, in such a way that even numbers inside the envelope correspond to the intervention group and odd numbers belong to the control group.

Researchers will visit the Seyyed Al-Shohada Hospital in Urmia after obtaining official approval from the Ethics Committee of Urmia University of Medical Sciences. After introducing the research, explaining the objectives and methods to the patients, eligible individuals will be selected. Upon their agreement to participate, informed written consent will be obtained from both men and their spouses. Subsequently, the couples’ phone numbers will be collected for scheduling counseling sessions. Researchers will emphasize the importance of couples attending counseling sessions together.

A couple participated in sessions within 6 groups, each consisting of 8 members, held weekly for 60 min. After collecting participants’ phone numbers, it was arranged for them to be prepared for 6 sessions of sexual counseling based on the CHARMS method. The intervention program was designed based on the CHARMS empowerment program and following similar studies [17].This intervention includes: (1) sexual education and counseling for spouses of patients with heart attacks, (2) educational and supportive intervention for heart attack patients by researchers and nurses in the cardiac rehabilitation program, (3) delivering informative booklets to patients, and (4) providing pamphlets on the topics of each session to increase awareness among heart attack patients and their spouses.

The content of each counseling and educational session was compiled by the research team from books, articles, websites, and reputable sources such as: European Society of Cardiology and American Heart Association [26–31] (Table 1).

After preparing the counseling content for each session, we validated the developed content using the Delphi method based on feedback from reproductive health and cardiology experts at Urmia University of Medical Sciences. These experts possessed the necessary knowledge and skills in sexual counseling and essential care for heart patients. We conducted three rounds of questionnaires with a panel consisting of three cardiology specialists and three reproductive health specialists.

Interventions at the Cardiac Rehabilitation Center of Seyed Al-Shohada Hospital will be conducted with the presence of patients suffering from heart attacks and their spouses. The intervention will be in the form of discussions, group consultations, and individual consultations if needed, which will be presented at the end of the session.

The sessions will be managed by researchers who have the necessary skills and knowledge regarding sexual counseling. The topics of each session will be presented to the participants by the researchers. In this regard, the researcher will facilitate and guide the sessions. During the intervention, tools such as pamphlets, PowerPoint presentations, speeches, and couples counseling will be used to enhance the effectiveness of the intervention program.

First, the demographic information form is completed by the control and intervention groups, and then other questionnaires are completed by the women of both groups (pre-test). One month after the end of the intervention, the questionnaires will be completed again by women in the control and intervention groups (post-test).

**Table 1 Tab1:** Contents of counseling sessions based on the CHARMS method

No	The content of the session	Type of consultation
First	With a focus on establishing communication and building trust and collaboration between couples, evaluating the mental, emotional, and physical health of individuals, identifying their sexual problems, informing couples about the session structure and setting goals, educating on the sexual cycle, and familiarizing them with sexual performance and the internal and external organs of men and women. Defining sexual desire, arousal, lubrication, and orgasm, as well as familiarizing them with the sexual response pattern and explaining the physiological changes in men and women during sexual activity, including sexual positions.	Group
Second	Counseling and providing information about cardiovascular diseases and symptoms, general and sexual consequences on the individual and their impact on the life of patients.	Group
Third	Counseling and providing information on the impact of cardiovascular disease on reducing sexual desire, lack of sufficient communication skills in sexual relationships, misconceptions about sexual relationships, providing information and education on coping with shame and deciding to resolve it, providing information on sexual aspects of life and training strategies to enhance marital satisfaction, providing necessary information and education on sensory focus techniques. Providing information on expressing feelings and beliefs about sexual behaviors and teaching problems-solving skills.	Group
Fourth	Consultation and provision of information on identifying the root causes of decreased sexual desire, offering solutions, strengthening empathetic communication, sexual discourse with a partner, explaining the secrets of sexual attraction, assisting in maintaining verbal and emotional relationship with a spouse, emphasizing the importance of lovemaking and romance, warning signs of heart disease during or after intimacy.	Group
The fifth	Collaborative contract writing technique to articulate needs and expectations in sexual relationships, clarifying expectations, correcting misconceptions and myths about sexual relationships, guidance on creating a structured timeline for noting thoughts and mindset during desirable and unpleasant sexual experiences, aversion, muscle tension, and emotional pressures. Household responsibilities, addressing potential inquiries.	Group
The sixth	Review of previous materials and nutritional recommendations, sleep hygiene education, performing stretching exercises and sports, recommending daily walks, bedroom environment, teaching alternative positive thinking and stopping negative thoughts.	Group

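### The allocation section divides 45 + 45 couples, the requirement before attrition, while the Abstract and the sample-size section plan 50 per arm; following it loses the whole attrition allowance

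*Protocol article*

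**What the plan says.** Three places in the protocol article give the number of couples.

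- **Abstract, Method:** participants are randomly allocated to "control (50 couples) and intervention (50 couples" in each case, so 100 couples in total.
- **Methods, Sample size:** "the sample size was estimated to be 45 couples in each of the two intervention and control groups". The next sentence allows for attrition in each study arm and concludes that "approximately 50 couples will be selected and included in the study".
- **Methods, Sampling and data collection:** the sample is "divided into two groups: intervention (45 couples) and control (45 couples) based on even and odd numbers in sealed envelopes", so 90 couples in total.

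On delivery, the Abstract says "Couples in 6 groups of 8 members each will attend counseling sessions", and Sampling and data collection repeats six groups of eight members. The word for a group member is not defined as a couple or a person.

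**The concern.** The Abstract and the allocation section describe the same act, dividing couples between arms, with different numbers. The allocation section uses the figure that the sample-size section treats as the requirement before attrition. It is also the operational text, which tells staff how many couples to divide by envelope.

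Three things depend on this number: when recruitment stops, the denominator against which attrition is judged, and whether the planned power survives loss. With two targets, a trial that stops at 90 couples could be called either complete or 10 couples short.

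Some loss is foreseeable. The exclusion criteria remove couples who miss more than one session, withdraw or move city, and the post-test comes one month after the intervention ends.

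**Working it through.** **Inputs, all from the Sample size section.** "Considering an alpha of 0.05 and 80% power"; the formula uses 1.96, so the test is two-sided. The score "before intervention was 2.47 ± 81.30" and "after intervention was 2.28 ± 82.70". Mean and SD are printed in reverse order, so the means are 81.30 and 82.70 and the SDs 2.47 and 2.28. The difference is 82.70 − 81.30 = 1.40.

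**Step 1: reproduce the plan's 45.** For two independent means with the normal approximation:

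n per arm = (z₀.₉₇₅ + z₀.₈₀)² × (SD₁² + SD₂²) / difference²

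- Variance sum: 2.28² + 2.47² = 5.1984 + 6.1009 = 11.2993.
- With exact normal quantiles, n = 45.25. With the plan's rounded 7.89, n = 7.89 × 11.29 / 1.96 = 45.4.

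The stated 45 is therefore reproduced. It is the number that must be analysed, with no slack: strict rounding up would give 46. The printed formula shows 0.58 for the power quantile and has no brackets around the variance sum. These are separate typographical matters, and the 45 follows once the sum is bracketed and the printed 7.89 is used.

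**Step 2: the allowance.** The allowance is 50 − 45 = 5 couples per arm, 10 in total. Since 45/50 = 0.90, it corresponds to 10% loss. The protocol states no rate, so 10% is an inference and the range below is needed.

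**Step 3: power by number randomised and by loss.** Power ≈ Φ(1.40 / √(11.2993 / m) − 1.96), where m is the number analysed per arm. For m = 45: √(11.2993/45) = 0.501, 1.40/0.501 = 2.79, and Φ(0.83) = 79.8%.

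| Assumed loss | From 45: analysed | Power | From 50: analysed | Power |
|---|---|---|---|---|
| 0% | 45 | 79.8% | 50 | 83.8% |
| 5% | 42.75 | 77.7% | 47.5 | 81.9% |
| 10% | 40.5 | 75.5% | 45 | 79.8% |
| 20% | 36 | 70.5% | 40 | 75.0% |

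The noncentral t distribution gives slightly lower values and the same picture: 83.0% at 50, 78.9% at 45, 75.0% at 41 and 73.9% at 40.

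**Step 4: group places.** 6 × 8 = 48. If a member is a couple, that is 3 more than 45 and 2 fewer than 50.

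**The case against.** The strongest reply is that the intended number can be recovered. The sample-size section derives 45 and raises it to about 50, and the Abstract repeats 50 + 50. The 45 in the allocation section therefore looks like a figure that was not updated, not a rival design. With no loss, 45 per arm gives essentially the planned power, and at the implied 10% loss the cost is about 4 points. All of this stands and limits the size of the point. It does not remove the contradiction. The 45 + 45 cannot be read as the number analysed, because the sentence describes how couples are divided by envelope. The qualifier on the 50 does not bridge the gap either, because 45 is the figure before the allowance is added.

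It could also be argued that about 50 couples in the sample-size section means a total. With 45 required in each arm and 50 + 50 in the Abstract, it can only mean 50 per arm.

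A reader might infer something stronger from the group sizes: that a member is one person, that the sessions therefore seat only 24 couples, and that power drops sharply as a result. The text does not support this. The Abstract makes couples the subject of the sentence, so eight couples per group is the natural reading, and 48 couples is close to about 50. Nor does any section say that a couple without a place would leave the analysis. What remains is an undefined word and a gap of two couples, which slightly larger groups could absorb.

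**Conclusion.** The point holds as an error in the number to randomise. The allocation section carries the figure before attrition and conflicts with the Abstract and the sample-size section. If it is followed, all 5 couples per arm of the attrition allowance are lost.

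The consequence is modest but consistent. At equal loss, randomising 45 instead of 50 costs about 4 to 5 percentage points of power. From 45, power starts at about 79-80% and moves further below the stated 80% with any loss.

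These figures rest on the protocol's own difference and SDs, a two-sided 5% test of two independent means, equal loss in both arms, and loss rates of 5% to 20% that are assumptions. The wording on group membership is a minor clarification and does not establish a shortage of places.

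**What to change.** - In Sampling and data collection, change 45 and 45 to 50 couples randomised per arm (100 in total), in line with the Abstract and the Sample size section.
- In Sample size, say explicitly that 50 is per arm, and state the attrition rate assumed. If 45 analysed from 50 randomised is what was meant, that rate is 10%.
- In the Abstract and in Sampling and data collection, say whether a group member is a couple. If so, reconcile the 48 places with the 50 couples allocated to counselling.

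The cost is a text correction, to be made before allocation. It means 10 more couples than the allocation section gives, but none beyond the number already planned in the Abstract and the sample-size section.

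### Only the intervention arm is counselled in groups, but the sample size and between-arm tests assume independent women, so level and power depend on a within-group correlation the article does not give

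*Protocol article*

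**What the plan says.** **Allocation.** Under Sampling and data collection, couples are allocated individually: "The participants will be asked to choose an envelope", with even numbers leading to counselling and odd numbers to control. No groups are described for the control arm.

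**Delivery.** The same section says "A couple participated in sessions within 6 groups, each consisting of 8 members, held weekly for 60 min", and the Abstract repeats the six groups of eight. The format is described so: "The intervention will be in the form of discussions, group consultations, and individual consultations if needed". Table 1 labels all six sessions as group sessions. Only the wives complete the outcome questionnaires.

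**Sample size.** "Considering an alpha of 0.05 and 80% power, the sample size was estimated to be 45 couples" in each arm. The formula is the one for two independent means, with no design effect. Its inputs are that sexual satisfaction "before intervention was 2.47 ± 81.30 and after intervention was 2.28 ± 82.70" in one arm of a cited study. For attrition, "approximately 50 couples will be selected and included in the study". The Abstract allocates 50 couples to each arm, and Sampling and data collection allocates 45.

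**Analysis.** "Independent t-tests/Mann-Whitney tests will be employed to compare normal/abnormal quantitative variables between two groups", with chi-square tests for qualitative variables. Regression is left as an option with no stated trigger or model. Grouping is not mentioned.

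**The concern.** This is a partially nested design: randomisation is by couple, after which one arm is treated in groups and the other is not. Women who share six weekly discussions about trust, shame and sexual misconceptions may move together. If they do, the mean of the intervention arm varies more than the independent-samples standard error allows.

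Two things are then at stake. The planned post-test comparison rejects a true null more often than the stated 5%. And an analysis that holds the 5% level needs more couples than the formula gives. If nobody records which couple sat in which group, the correct analysis may be impossible afterwards.

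**Working it through.** **Inputs.** From Sample size: difference 82.70 − 81.30 = 1.40, SDs 2.28 and 2.47, two-sided alpha 0.05, power 80%. These are taken at face value. From Sampling and data collection: six groups of eight members. Assumed: an intra-group correlation (ICC) of 0.02 to 0.10, because the article gives none.

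**Step 1: reproduce the 45.** n = (1.96 + 0.84)² × (2.28² + 2.47²) / 1.40² = 7.84 × (5.198 + 6.101) / 1.96 = 45.2. The printed 0.58 is not the normal quantile for 80% power, and the printed numerator lacks a bracket; these are separate matters. With 45 per arm, SE = √(11.299/45) = 0.501 and 1.40/0.501 = 2.794. Power = Φ(2.794 − 1.96) = 79.8%. Independence therefore leaves no margin.

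**Step 2: allow for grouping in one arm.** With m women per group, the intervention-arm variance is multiplied by DE = 1 + (m − 1) × ICC and the control arm is unchanged. For equal arms and a common SD, the variance of the difference grows by R = (DE + 1)/2. Then:

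- true level of the plain test = 2 × [1 − Φ(1.96/√R)]
- power of an analysis that respects grouping, 45 per arm = Φ(2.794/√R − 1.96)
- n per arm for 80% power = 45.25 × R (45.25 is Step 1 with unrounded quantiles)

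Example with m = 8 and ICC 0.05: DE = 1.35 and R = 1.175. The level uses 1.96/1.084 = 1.808, giving 7.1%. Power is Φ(2.577 − 1.96) = 73%.

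| Couples per group | ICC (assumed) | DE | R | True level | Power at 45 per arm | n per arm for 80% |
|---|---|---|---|---|---|---|
| 8 | 0.02 | 1.14 | 1.070 | 5.8% | 77% | 48.4 |
| 8 | 0.05 | 1.35 | 1.175 | 7.1% | 73% | 53.2 |
| 8 | 0.10 | 1.70 | 1.350 | 9.2% | 67% | 61.1 |
| 4 | 0.02 | 1.06 | 1.030 | 5.3% | 79% | 46.6 |
| 4 | 0.05 | 1.15 | 1.075 | 5.9% | 77% | 48.6 |
| 4 | 0.10 | 1.30 | 1.150 | 6.8% | 74% | 52.0 |

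**Step 3: which group size?** Eight members may be eight couples or eight persons (four couples, so four women with outcomes). Six groups of eight couples hold 48, which matches neither 45 nor 50. Six groups of four couples hold 24, about half the arm. The four-couple rows therefore assume enough extra groups to place the whole arm.

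**Step 4: does the rise to 50 cover it?** 50/45.25 = 1.105. With m = 8, R = 1 + 3.5 × ICC reaches 1.105 at an ICC of about 0.03. Fifty per arm holds 80% only up to there, and only with no attrition, which is what the extra couples are meant to cover.

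**Step 5: simulation.** With six groups of eight against 48 controls (40,000 trials per setting), the plain t-test rejects a true null in 6.8% and 9.0% of trials at ICC 0.05 and 0.10, in line with the table. A group-mean test with Satterthwaite degrees of freedom holds 5.1% and 5.4%, with power of 69% and 62%. The normal approximation at 48 per arm gives 76% and 70%. Having only six groups already costs about 5 points at zero correlation (82% by normal approximation, 77% simulated). That part is not caused by correlation.

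**The case against.** The strongest reply is that the article gives no group-level ICC, so nothing shows that the correlation is more than trivial. This stands as to size. At ICC 0.01 with eight couples per group, the level is only 5.4% and power 78%. It does not remove the mismatch between delivery and analysis.

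Three stronger readings are tempting, and the article does not support them:

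- **That p-values will be too small.** This holds only if the ICC is positive. The coefficient of 0.88 under Validity and reliability of questionnaires is an instrument property and cannot be used here. Nor does the text say that each group keeps its own facilitator or a fixed membership; it says only that researchers run the sessions. The argument rests on shared group discussion alone.
- **That the planned t-test loses power.** In the simulation it still rejects in about 79% and 78% of trials under the alternative at ICC 0.05 and 0.10, but at an inflated level. The loss applies to an analysis that respects grouping.
- **That every planned comparison is affected.** Pre-test comparisons between arms are not, because counselling has not started.

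It may also be said that such detail belongs in an analysis plan, or that the optional regression covers it. But the article itself fixes the formula, the sample size and the tests, and an ordinary regression without a group term has the same fault. It is fair that six groups estimate a group variance poorly; that is a cost of the remedy.

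**Conclusion.** The point holds in conditional form. The article describes group delivery in one arm and fixes a sample size and between-arm post-test comparisons that assume independence. Any positive ICC pushes the plain test above 5% and takes a grouping-respecting analysis further below 80% power at 45 per arm.

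Over the assumed ICC range of 0.02 to 0.10, the level is 5.8% to 9.2% and power 77% to 67% with eight couples per group. With four couples per group the figures are 5.3% to 6.8% and 79% to 74%. They rest on the normal approximation, equal arms, a common SD and the plan's own effect size. Small-sample degrees of freedom lower power further. The direction is firm once the ICC is positive, but the size cannot be settled from the article.

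**What to change.** 1. State the group size in couples, and reconcile six groups of eight with the 45 and 50 couples per arm given elsewhere.
2. Record each intervention couple's counselling-group number.
3. Compare post-test scores between arms with a partially nested linear mixed model: arm and pre-test score as fixed effects, a random counselling-group effect in the intervention arm only, and Satterthwaite or Kenward-Roger degrees of freedom.
4. In Sample size, restate power over an ICC range of 0.02 to 0.10, labelled as an assumption, for the confirmed group size. This does not require enrolling more couples.

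The cost is one extra variable and revised wording. The price in the results is a somewhat larger standard error, a lower stated power, and a group variance estimated imprecisely from six groups. Adjusting for the pre-test score may win back some precision, but the article gives no pre-post correlation, so no gain should be counted on in the power statement.
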